## Abstract

**Background:**

Canada has one of the highest rates of multiple sclerosis (MS) in the world. Treatments and supports for people with MS (PwMS) have become increasingly complex, requiring individualized and adaptive care. Specialized NPs provide advanced skills to those with complex medical conditions, with potential to enhance the health, functioning, and quality of life for PwMS. This study aims to determine the effect of a Nurse Practitioner (NP) on depression and anxiety levels in PwMS.

**Methods:**

We will perform a parallel randomized controlled trial. PwMS who are followed by general private-practice neurologists will be randomly assigned to the intervention group (NP-led care) or the ‘usual care’ control group (general neurologist or family physician and registered nurse support). In the intervention group, the NP will assess and provide care to the MS patient and their caregiver at a baseline visit, with 3-month and 6-month follow-up visits. PwMS in the control group will receive usual care provided by their community neurologists or family physicians with the standard assistance provided by registered nurses experienced in MS care. The primary outcome will be the difference in change in the patient’s anxiety and depression scores as measured by the validated Hospital Anxiety and Depression Scale (HADS) questionnaire at 3 months. Secondary outcomes will include difference in change in HADS at 6 months; Modified Fatigue Impact Scale scores (MSIF) at 3 and 6 months; EQ-5D scores at 3 and 6 months; caregiver health-related quality of life in MS measures (CAREQOL-MS) at 3 and 6 months; number of visits and phone calls to healthcare professionals recorded by patient, and satisfaction with NP-led care vs usual care measured by the validated Consultant Satisfaction Questionnaire.

**Discussion:**

Findings from this study will contribute to exploring benefits of advanced nursing practitioner interventions for PwMS followed by general neurologists and family physicians in a community setting. It will provide evidence of the benefits of NP-led care for PwMS and offer an alternative healthcare resource for management of MS.

**Trial registration:**

ClinicalTrials.govPro00069595. Retrospectively registered on June 26, 2020. Protocol version: January 2017, version 1.

**Supplementary Information:**

The online version contains supplementary material available at 10.1186/s13063-021-05726-3.

## Background

Multiple sclerosis (MS) is the leading cause of non-traumatic disability in young adults [1–4]. It is most commonly diagnosed in people between the ages of 15 and 40, with visible symptoms such as walking difficulties, balance, coordination, and double vision, in addition to unseen symptoms such as fatigue, cognitive issues, depression, anxiety, and pain. These symptoms usually progress over a lifetime, accumulating disability that limits functioning [5–10]. Canada has one of the highest prevalence of MS in the world [1, 2], with Alberta having the highest rate of MS in Canada (340/100,000 population) [5]. Since MS onset most often occurs in early adulthood [4, 6, 7], persisting and progressing throughout people’s lives, it becomes important for healthcare systems to address and adapt to their individual needs, and to keep people with MS (PwMS) as functional as possible [4, 5, 10, 11].

The global approach to treating and supporting PwMS has become multidisciplinary, multi-pronged, and increasingly complex, as MS impacts a person’s physical, psychological, and social well-being [12]. There is strong evidence that PwMS prefer multidisciplinary care [13], similarly viewed as essential by international MS experts [4, 14]. Since every individual’s experience of having MS is unique, the education, treatments (symptomatic and disease-modifying therapies), and counseling provided should be tailored and personalized, adapting as their MS advances [13]. The resources (e.g. education, counseling, support, care) provided to PwMS should also evolve and change as a person’s MS progresses and their needs change [15]. However, despite this recognition for multidisciplinary and personalized care, healthcare and patient outcomes for PwMS in the twenty-first century has not advanced [3]. Multiple studies have reported a number of unmet care needs for PwMS: these areas include healthcare delivery [15–17], education, counseling, psychological support [18, 19], and in support provided to their informal caregivers [19–21]. In 2020, a study of over 1000 PwMS found a correlation between those that had a high level of unmet health and social care needs and lower health-related quality of life [22]. They also identified that all the domains of the Euro Quality of Life Measurement (EQ5D) were important in measuring quality of life for PwMS. The EQ5D quality of life measure is commonly used in the MS population [23]. The EQ5D-3 L includes the five dimensions: mobility, self-care, usual activities, pain/discomfort, and anxiety/depression and each dimension has 3 levels: no problems, some problems, and extreme problems [24]. Quality of life assessments are important measures in studies in multiple sclerosis since there is no cure for MS and because management and interventions in MS are symptomatic, disease modifying in attempting to stabilize progression, and rehabilitation-related [23]. PwMS have reported lower quality of life compared to the general population, even in those with mild disability [25–30].

Depression has been identified as one of the most important factors determining quality of life for PwMS [31–35]. A recently published systematic review and meta-analysis around the prevalence of depression and anxiety in PwMS, reported prevalence of depression and anxiety to range from 14 to 54%, estimating the pooled mean prevalence of depression to be 30.5% (95% CI 26.3–35.1%), and to be 22.1% for anxiety (95% CI 15.2–31.0%) [36]. Included studies reported mixed findings about whether the degree of MS disability correlates with the presence of depression and anxiety [36]. One study concluded that people with progressive MS may be more likely to experience depression compared to those with relapsing remitting MS [37]; however, another study reported less tendency for people with primary progressive MS to have depression compared to other types of MS [38], and multiple researchers have reported the presence of depression in PwMS to be independent of disease course or level of disability [36, 39–41]. Thus, depression and anxiety are highly prevalent in PwMS, significantly affect quality of life for PwMS, and are often present beyond physical disability [41], reported to be common even at the time of MS diagnosis, and possibly increase with the duration of living with MS. [41, 42] One prospective observational study of functioning and use of healthcare services by PwMS with or without depression reported that those with depression but milder overall disability tended to use more healthcare services than those without depression [43]. Both depression and anxiety have been identified as important comorbidities for PwMS, linked to other MS symptoms such as fatigue, and associated with decreased adherence to taking disease-modifying therapies [44]. The presence of psychiatric comorbidities such as depression and anxiety has been associated with increased risk of mortality and suicide [29]. However, despite the high prevalence, one study of clinical and administrative data for 859 PwMS found that diagnoses of depression and anxiety are underdiagnosed in PwMS: one-third with current symptoms of depression and two-thirds with current symptoms of anxiety were not correctly diagnosed as having these conditions [28]. This was supported by another set of researchers who found that even when 85% of PwMS were treated for depression, many still struggled with symptomatic depression, leading the authors to conclude that their depression was undertreated [45].

Depression and anxiety treatments for PwMS include antidepressant/anti-anxiety medication, counseling, increased psychosocial supports, cognitive behavioural therapy, self-management strategies, and referrals to psychologists, therapists, and psychiatrists [30, 46–49]. The meta-analysis of interventions for depression in PwMS concluded that both pharmacologic and psychologic interventions for depression were effective in PwMS, but that the data was insufficient around anxiety to definitively determine the efficacy of anxiety treatment strategies [47]. Another meta-analysis of the effects of clinical interventions upon health-related quality of life measures in MS in 2012 reported that psychological interventions to improve mood in MS had the highest effect upon quality of life amongst clinical interventions [30]. A more recent systematic review in 2017 explored all self-management strategies for PwMS to manage depression, anxiety, and quality of life, concluding that there appears to be efficacy, but that more evaluation is needed to fully conclude the efficacy of these types of interventions [49]. Pharmacologic and non-pharmacologic approaches to depression and anxiety, counseling, psychosocial support, in addition to referrals to psychologists and psychiatrists, coordination of care, and patient education fit within the scope of NP approaches to MS care [50–54].

In northern Alberta, Canada, private-practice, community general neurologists and family physicians provide care to approximately 2000 PwMS outside of a tertiary multidisciplinary clinic setting with a wide catchment area extending across Central and Northern Alberta, Northern BC, Saskatchewan, and Northwest Territories. It is challenging for general neurologists and family physicians to balance care of PwMS with the pressures of busy office practices in a fee-for-service setting [14, 55, 56]. Thus, it is important to look at look at ways to enhance care of PwMS through multidisciplinary teams containing MS specialized nurses, especially nurse practitioners who practice with increased autonomy and expertise [14, 56].

A 2020 integrative review identified three key themes required of the role for MS specialized nurses: (1) longitudinal care co-coordinator; (2) care provider; and (3) expert resource [51]. In an audit questionnaire conducted in 2013, 83% of PwMS indicated that they preferred contacting the MS specialized nurse above other health professionals as they felt the MS nurse understood their specific condition better than their other healthcare professionals, such as their family doctor, neurologist, physiotherapist, occupational therapist, or other [57]. It has been suggested nurse practitioners (NPs) with their expertise in chronic disease management are well-placed to provide comprehensive care to PwMS [52–54]. In addition, having NPs to enhance the multidisciplinary team could potentially provide healthcare cost-savings: in the USA, NP-led care was reported to be cost-saving of 11–29% in comparison to physician-led care [58, 59]. This was supported by a systematic review looking at the cost-effectiveness of nurse practitioners in both primary and specialized ambulatory care, including eleven trials [60]. They found that while nurse practitioners demonstrated equivalent or better patient outcomes in the primary care setting. There were fewer studies for the specialized ambulatory care setting: NP care in the specialized ambulatory care setting was similarly demonstrated to be more cost-effective, but with too few studies to make concrete conclusions [60].

As noted by the systematic review in 2015, there have been only a handful of randomized controlled trials comparing NP-led care vs usual care for people with chronic diseases, with different models: in the primary care setting; in the specialized setting instead of physician specialists, but backed up by specialist physician support when needed; and as an add-on to a physician specialist in a multidisciplinary setting [60]. The few studies adding an NP into the specialized setting, either delivering care instead of the specialist physician (still backed up by specialist physicians when needed), or as an overall add-on to the multidisciplinary specialty teams, did show improved patient outcomes. One study directly compared NP care to dermatologist care for children with eczema [61, 62]. In this study, the NP independently evaluated children with eczema, wrote prescriptions and approached the dermatologist for support as needed. NP care was determined to be equivalent to that from the dermatologist in decreased symptoms and improved quality of life in addition to higher parent satisfaction [61, 62]. A second randomized trial compared NP to gastroenterologists in performing screening colonoscopies [63]. Again, the NP had access to a gastroenterologist for support, but worked independently. NP care resulted in better adenoma and cancer detection and higher patient satisfaction scores [63]. There were five superiority trials included in the review, where an NP was added to what was considered usual care (physician-provided care) [64–70]. Specialty areas included multidisciplinary care for lipid control and coronary heart disease [64, 65], type II DM management [66], hypertension and diabetes management within a tertiary hospital setting [67], and for patients with medically unexplained symptoms and a previously high utilization of primary care services [68–70]. Another randomized controlled trial allocated people with Parkinson’s disease to an intervention group (consisting of a movement disorders specialist, specialized Parkinson’s disease nurses, and a social worker) or a control group (comprised of care from general neurologists) for an 8-month intervention period showed that those people with Parkinson’s disease in the intervention group reported improved quality of life as compared to those participants looked after by general neurologists. In this study, usual care was determined by the general neurologist with no standard approach to the frequency of visits or other interventions. The researchers acknowledged limitations in study design, including the inclusion of a movement disorders physician specialist to the intervention team delivering patient care, the possibility of more neurological services being provided to the intervention group as compared to the control group, and not being able to know which services were offered to those in the control group. However, those in the multidisciplinary specialty team intervention reported better Parkinson’s measurement outcomes compared to those in the control group [71]. Finally, Broderick and colleagues examined NP delivery of pain coping skills in optimizing management strategies for people living with chronic pain [72]. They found that those who had received the intervention of NP delivered pain coping skills reported better pain control, coping, and use of pain medication. However, it is unclear as to whether the involvement of the NP or the learning of the pain coping skills led to improved pain measure outcomes [72].

This randomized control trial (RCT) design is similar to a protocol which studied the impact of NP-led care for people with atrial fibrillation, designed by Smigorowsky et al. [73] The RCT protocol written by Smigorowsky et al. used a similar design as this RCT with validated objective patient-reported outcome surveys, in addition to using the same consultant satisfaction survey as an outcome. The study by Smigorowsky et al. was carried out within the same Alberta Health Services clinical setting, with an intervention design established as acceptable to the Alberta Health Services clinical administrative managers, to the same overall type of patient population in terms of demographics, with the same mix of rural and urban backgrounds [73].

Usual care by general community neurologists in the current northern Alberta setting consists of variable visits and phone calls to the family physicians and the general neurologist’s office, with access to rehabilitation services and therapies, as determined by the general neurologist or family physician. In ‘usual care’, family physicians and general neurologists do not have ready or extensive access to MS specialized nurses, for counseling of PwMS about diagnosis, coping strategies, relapse identification and treatment, and education on symptoms of MS and disease-modifying therapies. At the time of this study, some general neurologists in the greater Edmonton area do have the option of having registered nurses aid their clinic on a designated day per week, with limited scope of practice in rooming PwMS, checking their medications, and aiding in disease-modifying therapy initiation and renewals. In contrast, NPs perform independent holistic approach to PwMS, counseling, education around coping strategies, disease-modifying therapies and side effect management, identification of MS symptoms such as depression and anxiety, with independent prescription of symptomatic medications such as antidepressants, independent ordering of investigations such as bladder function, and independent referrals to psychologists, home care resources, social workers, and rehabilitation programs [54]. There is an established specialized NP in the tertiary MS clinic in Edmonton that performs independent assessment of PwMS, prescribing of symptomatic medications, identification and treatment of relapses, referrals to homecare services, urologists, rehabilitation, social workers, and for psychologist support in addition to referral to group cognitive behavioural therapy classes. The NP undertakes comprehensive one-on-one and group education around disease-modifying therapies, coping strategies with MS, lifestyle strategies, and symptomatic self-management strategies, as identified in this publication around the role of MS specialized NPs [51]. MS specialist neurologists in the tertiary MS clinic are accessible to the MS NP for support and questions. In the current ‘usual care’ setting, community general neurologists and family physicians do not have access to a similar specialized MS NP.

Our research question is to evaluate whether the add-on care by a NP is superior for PwMS compared to their usual medical care in a generalist medical setting of general neurologist and/or family physicians. This study aims to evaluate the add-on effects of NP-led care for PwMS on their depression and anxiety levels compared to ‘usual care’ (community neurologists’ care or family physician). We hypothesize that PwMS whose care is managed by an NP would have less depression and anxiety from baseline (as measured by the Hospital Anxiety and Depression Scale—HADS) at 3 months [47, 74–76]. The objectives of this study are
To evaluate the add-on effects of NP-led care for PwMS on their depression and anxiety levels at 3, 6, and 12 months compared to ‘usual care’,To measure quality of life for PwMS and their caregivers and fatigue levels,To evaluate the number of outpatient healthcare visits and phone calls, andTo measure patients’ satisfaction of the care provided in both groups.

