## Methods

This study has been designed as a parallel RCT with two equal-sized groups (see Fig. 1). We used the SPIRIT reporting guidelines; please see the Additional file 1 for the SPIRIT checklist [77]. Figure 1 outlines the study protocol procedure and Table 1 provides the study timeline, as per SPIRIT guidelines [77]. Participants will be randomized to the add-on nurse practitioner-led care (NP-led care arm) as the intervention arm of the study over a 6-month period vs their usual medical care comprising the control arm (usual care arm), consisting of their community neurologist and/or family physician and registered nurse (RN). Usual care will vary amongst community neurologists’ practice, but typically involves annual visit.

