### Intervention arm (NP-led care arm)

Participants randomized to the intervention group will be contacted by the NP to be scheduled for an appointment with the NP within 4 to 6 weeks from the date of the referral. The NP consultation will include patient history, physical examination, symptomatic management strategies as appropriate (e.g. bladder and bowel management strategies, fatigue management, depression, anxiety, spasticity), discussion of mental and physical health resources for symptomatic treatment, support, physical and mental health resources to optimize functioning (e.g. home care or physical/occupational therapy referral), and quality of life interventions. The NP will follow up with the patient either in person, by phone, or by videoconferencing at 3 months, at 6 months, and again at 12 months. The NP will be accessing the electronic medical record offered by Alberta Health Services [85] to maintain charting consistency in diagnostic testing, appointments, and communications [85]. During the visits, the NP will check the completion of study questionnaires at the appropriate timepoints, and ask the participant +/− caregiver about the completion of questionnaires. If the NP feels that he/she needs help in managing a participant, he/she will refer the participant back to the community neurologist and/or family physician in charge of the participant at any time throughout the study. As mentioned above, the NP will be sending summaries of visits to the neurologists and family physicians and may ask questions of the community neurologists as to their preferences in treatment approaches as needed (e.g. disease-modifying therapies, treatment of relapses with steroids) in individual situations. This fits within the multidisciplinary model of MS care, seen in MS clinics [11].

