### Control arm (usual care arm)

PwMS who are randomized to the usual care arm (community neurologist or family physician and registered nurses) will be contacted by the NP to be scheduled for an NP appointment at 6 months after study conclusion. Thus, every PwMS is given the opportunity to access NP care after their involvement in the study has concluded. During the 6-month period, patients randomized to the control group will receive usual care from community neurologists or family physicians and MS registered nurses. The care will be delivered according to standard practices, and follow-up visits will be conducted according to the various clinical practices of the neurologists’ or family physicians’ clinics. For those in the usual care arm, the EPICORE Centre’s research team will contact the participant +/− caregiver about the completion of questionnaires at the appropriate timepoints. The participant diary will be collected by the NP when the participant in the usual care arm has finished the study and is offered a follow-up visit with the NP outside of the study. If family physicians wish to have more urgent patient assessments, they will be offered the additional opportunity of referring the patient to a community neurologist or a NP outside of the study if they feel that the patient cannot wait 6 months for MS specialized care; these patients will also be excluded from being involved in the study.

Participants are able to initiate contact with their usual community neurologist and/or family physician in either arm of the study, throughout the study as they need. Participants will continue to be followed by their family physicians and regular community neurologists during the study, in either arm. For those in the NP-led care arm, they will receive additional care by the NP during the 6 months of the study duration.

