A longer-term follow-up will be conducted at 12 months to evaluate the long-term differences of the 6-month intervention in change of the patient-reported outcome measures (HADS, MFIS, EQ5D, and CAREQOL-MS). By then, all participants would have seen the NP, and the goal of the late follow-up would be to see if there was (1) long-term impact of the 6-month NP intervention (from those in the original intervention group), and (2) to check the larger patient number impact of the NP intervention upon those within the control group.

If participants score very low or severe on their scales around anxiety, depression, fatigue, quality of life, and/or their caregivers score as very low on their questionnaire, their community neurologist and/or family physician will be contacted to see the participant on an urgent basis.

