### Dissemination, ancillary, and post-trial care

The longitudinal care for participants will continue throughout the study by their community neurologists and/or family physicians, in addition to the NP care in the intervention arm, as an add-on member of the care team, and described previously. Those in the control arm of ‘usual care’ will have an appointment with the NP at the end of the study, to receive the ‘add-on’ care from the NP for the 6 months after study completion, to ensure that every participant has access to seeing the NP. The results of this study will be shared with Alberta Health Services in consideration of their continuing to fund the position for supporting community neurologists in an outreach model going forward after the study. The hope is that the NP will continue in the outreach model established during the study. We are planning to have the NP position continue to operate within a 6-month intervention period, followed by referral of the PwMS back to their community neurologists and/or family physicians. This will enable the NP to take new patients over time, and not saturate the NP practice with long-term follow-ups. PwMS will always have the option of being re-referred back to the NP for another 6-month period.

This randomized control trial will be published once data analysis has been completed and all investigators will be invited to contribute to the manuscript. A copy of the publication and findings will be provided to the participants. At this time, there are no plans or arrangements for data sharing. We plan to disseminate the results at the European Committee for Treatment and Research in Multiple Sclerosis (ECTRIMS) conference, present to the Alberta MS Research Network, and to publish outcomes of the study in a peer-reviewed journal.

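### Objective 1 promises NP-led versus usual care at 12 months, but controls are offered NP care from about month 6, so the 12-month contrast is early versus delayed NP care

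*Protocol article*

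**What the plan says.** The objectives at the end of the Background begin: "To evaluate the add-on effects of NP-led care for PwMS on their depression and anxiety levels at 3, 6, and 12 months compared to" usual care. Twelve months thus stands beside 3 and 6 months as a time point for the same comparison.

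Elsewhere the article describes a randomised contrast that lasts half as long:

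- Methods describes NP-led care "as the intervention arm of the study over a 6-month period".
- The control-arm section says of the NP arm that "they will receive additional care by the NP during the 6 months of the study duration".
- Recruitment, Validity and reliability, and Limitations each place the controls' access to the NP at 6 months.
- The section on dissemination and post-trial care says controls then receive the add-on care "from the NP for the 6 months after study completion", which is roughly months 6 to 12.
- Outcomes says of the 12-month follow-up: "By then, all participants would have seen the NP". It gives two aims for that follow-up: the lasting effect in the original NP arm, and the NP's effect in the former controls.
- Validity and reliability presents the 12-month follow-up as a question about when the NP care was given.

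The intervention-arm section also lists NP follow-up "either in person, by phone, or by videoconferencing at 3 months, at 6 months, and again at 12 months".

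**The concern.** An objective names a contrast, and the design has to supply both sides of it. At 12 months it supplies only one. A result reported under Objective 1 as NP-led versus usual care would in fact compare people who had NP care in months 0 to 6 with people offered it in months 6 to 12. A null difference could be read as a faded effect, and a difference favouring the control arm as harm, although an effective NP could produce either. This matters in practice because the article says the results go to the health service that will consider whether to keep funding the NP position.

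The second 12-month aim has a related weakness. Once the controls cross over, no concurrent untreated group remains. Their change from month 6 to month 12 mixes any NP effect with natural course, regression to the mean and the effect of having waited.

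**Working it through.** **Who is exposed, and when**

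| Period | NP arm | Control arm |
|---|---|---|
| Months 0–6 | NP care plus usual care | Usual care |
| Months 6–12 | After the 6-month NP period (one section lists a further NP contact at month 12) | Offered add-on NP care |
| At month 12 | Has seen the NP | Has seen the NP |

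No cell at 12 months is usual care alone.

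**Inputs**

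- From the sample size section: difference to detect 1.5 HADS points, 100 per group, 80% power, two-sided alpha 0.05.
- SD: not printed in the article, so the figure of 100 per group cannot be independently reproduced. Solving backwards, SD = 1.5 × √(100/2) / (1.960 + 0.842) = 10.607 / 2.802 = 3.79. This is treated as an assumption, with a range of 3.5 to 4.5.
- r: share of the 1.5-point benefit that the NP arm still has at month 12. Assumed.
- c: share of the 1.5-point benefit that the control arm has gained by month 12, averaged over everyone in that arm. Assumed.

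**Expected 12-month difference**

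With benefit counted as positive for the NP arm, the observed between-arm difference is 1.5r − 1.5c = 1.5(r − c). Had the controls stayed on usual care, it would have been 1.5r. The contrast therefore falls short of the Objective 1 quantity by 1.5c, whatever r is. The two agree only if c = 0.

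**Chance of a significant result**

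Two-sided z-test, 100 per arm, standard error = 3.79 × √(2/100) = 0.54.

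| r | c | Difference | Significant for NP arm | Significant for control arm |
|---|---|---|---|---|
| 1 | 0 | +1.5 | 80% | about 0% |
| 1 | 0.5 | +0.75 | 29% | about 0% |
| 0.5 | 0.5 | 0 | 2.5% | 2.5% |
| 1 | 1 | 0 | 2.5% | 2.5% |
| 0.5 | 1 | −0.75 | about 0% | 29% |
| 0 | 1 | −1.5 | about 0% | 80% |

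The first row is the comparison that Objective 1 describes, with full retention and a true usual-care group. Over SDs of 3.5 to 4.5, the chance of a significant result favouring control runs from 33% to 22% at r = 0.5, c = 1, and from 86% to 65% at r = 0, c = 1.

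**Schedule**

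The sections on who delivers the intervention, on the control arm and on post-trial care limit NP care to 6 months. The intervention-arm section has NP follow-up "at 3 months, at 6 months, and again at 12 months". These do not agree on what the NP arm receives after month 6, and r depends on that. A single contact at month 12 would not restore a usual-care comparator.

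**The case against.** The strongest reply is that the article already discloses the crossover. Outcomes states it openly, and Validity and reliability frames 12 months as a matter of timing. The hypothesis and primary outcome concern 3 months, and the listed secondary comparisons stop at 6. On this view one loose phrase in an objectives list is at fault. Most of that stands, and it bounds the point. It does not rescue the objective, because the disclosure shows that the objective cannot be answered as worded.

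Four stronger readings might be inferred, and the document does not support them:

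- *The statistical analysis plans a 12-month test against usual care.* That section refers to different time points without naming 12 months. Its only examples are 3 and 6 months, and an unseen analysis plan may settle the matter.
- *Both 12-month aims are uncontrolled.* The first can be read as a between-arm comparison, and early versus delayed care is still a randomised contrast. Only the second is a plain before-after change.
- *An effective NP must look useless or harmful at 12 months.* That requires controls to gain at least as much as the NP arm retains. With r = 1 and c = 0.5 the difference still favours the NP arm.
- *Controls might not see the NP until a year in.* The phrase "to be scheduled for an NP appointment at 6 months after study conclusion" permits this, but Recruitment, Validity and reliability, and Limitations all point to month 6, so it is clumsy wording.

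**Conclusion.** Objective 1 is wrong as written for 12 months and should be changed. That no usual-care comparator exists then follows from the article's own text and needs no assumption. The 12-month between-arm difference is early versus delayed NP care, and it departs from the effect against usual care by 1.5c points: 0.75 if controls have gained half the planned benefit, 1.5 if they have gained all of it. Its sign can go either way. These sizes rest on the 1.5-point planning difference, on assumed values of r and c, and on the same full benefit being available early or late. The significance probabilities also rest on the back-solved SD.

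The NP's effect in former controls, taken from their own change after month 6, is uncontrolled. The randomised comparisons at 3 months (primary) and 6 months (secondary) are not touched by any of this.

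**What to change.** - Limit Objective 1, and any conclusion against usual care, to 3 and 6 months.
- Restate the 12-month between-arm comparison as early versus delayed NP care, in line with Outcomes and with Validity and reliability. It may still be tested as a randomised contrast under that label.
- State that any overall group-by-time test used to support a claim against usual care includes data through 6 months only.
- Report the month 6 to 12 change in former controls as an uncontrolled before-after change.
- Reconcile the NP follow-up listed at 12 months in the intervention-arm section with the 6-month NP care period given in the sections on who delivers the intervention, on the control arm and on post-trial care.

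The cost is wording in the protocol and analysis plan, and no data are lost. Trial status says that final quality assurance and analysis were still to come, so the change could be made before results were seen under the wrong label. The real price is that the trial can make no usual-care claim at 12 months, but the design could not support one in any case.
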